## Abstract

**Background:**

Children have alarmingly low levels of competency in fundamental motor skills (FMS) and high levels of physical inactivity. e:health interventions, interventions delivered electronically, are useful tools for intervention in the home through parents, but less is known about the effects of these interventions in early childhood education centers or settings. Therefore, we created the Motor skills At Playtime (MAP) e:health intervention (e:MAP) to be delivered in an early childhood education setting. The goals of this pilot study on e:MAP are to (1) determine the intervention effects on children’s FMS and physical activity and (2) explore the teachers’ perceptions and ability to facilitate e:MAP.

**Methods:**

This pilot study uses a pretest/posttest randomized cluster control design. We will recruit at least 64 children (3.5–5 years of age) enrolled in a single early childhood education center. Children will be randomly assigned at the level of the classroom to an e:MAP group (n~30) or a control group (n~30). Children in classrooms assigned to e:MAP will complete an 8-week intervention. We will collect measures of child FMS and physical activity, and teacher’s perceptions of the program before (pretest) and after the intervention (posttest). FMS measures include process (Test of Gross Motor Development-3rd Edition) and product-oriented scores. Physical activity will be assessed using a 7-day accelerometer wear protocol. Teachers’ perceptions will be assessed through a brief survey. Lastly, we will collect data on teachers’ ability to facilitate e:MAP through a daily survey.

**Potential significance:**

This study will yield novel insights into the effectiveness and feasibility of a health intervention in an early childhood education setting. Results from this work will expand our knowledge of how to harness e:health modalities, which have the potential to significantly expand the distribution and scalability of FMS interventions.

## 1. Introduction

Physical activity (PA) is an essential component of a healthy lifestyle yet alarmingly, only 20% percent of adolescents meet global physical activity recommendations [1]. The lack of PA is concerning as physical inactivity is linked to the manifestation of non-communicable diseases [2]. There are currently predicted to be 499.2 million new yet preventable noncommunicable diseases occurring by 2030 if physical inactivity is not addressed [2]. Consistent physical inactivity is seen across the lifespan, even in children. Currently, less than half of young children (i.e., children 3–5 years old) are meeting recommended PA guidelines [3, 4], and only 11.26% of children this age are meeting 24-hour movement guidelines, which include daily PA recommendations [5]. More locally, it is reported that in the state of Michigan, only 23% of children currently meet national PA recommendations [6]. Therefore, low levels of PA are both a global and local concern, and it is paramount we address this problem.

Children need competency in fundamental motor skills (FMS) to be active, but these skills are frequently overlooked in intervention and programmatic approaches to improve PA. FMS are gross motor skills that allow children to propel or manipulate their bodies and objects in space (e.g., running, throwing), and are building blocks for more advanced movement and engagement in PA [7–10]. FMS are reciprocally and inseparably linked to current and future PA [11–17]. There is a common misconception that these skills naturally emerge. However, evidence supports that FMS are not learned in the absence of instruction [18], and approximately 77% of children have delayed or impaired motor skills [19]. While a child at any age with a motor delay or impairment is concerning, the early childhood years (3–5 years) are an important developmental period and are part of the critical window of development for FMS [7–9]. Due to the developmental nature of these skills, skills learned during this period have the capacity to support future health, whereas failing to learn these skills at a young age could have negative ramifications for future health.

Despite this, young children are failing to learn FMS [18–21]. which is alarming from a public health and developmental perspective. Evidence-based and theoretically grounded interventions are needed to address these deficits. These interventions should capitalize on the conceptual and logical link between FMS and PA whereby engaging in FMS is engagement in PA and gaining FMS competency supports future PA engagement. Encouragingly, successful interventions have been used to teach FMS to young children [18, 22–26]. These interventions vary in terms of dose and implementation strategies; however, meta-analytic data supports that most successful interventions are shorter than 6-months in duration and implemented by non-school personnel (aka researchers) [22]. While it makes sense that individuals with expertise in motor development would implement highly effective interventions, limiting interventions to those implemented by personnel external to the early childhood education center or school setting limits the distribution of these programs. Therefore, there is a need to transition intervention efforts to those that can be completed within school or other settings (e.g., home) without the researcher’s presence. In the school setting, teachers likely play an important role in intervention implementation and outcomes. A recent review found that teachers can effectively implement physical education interventions/programs with small to moderate improvements in children’s (ages 5–12 years) FMS [27]. We have also seen several groups working to capitalize on the potential for teachers and deliver FMS interventions through teachers. For example, there is recent work to translate the Children’s Health Activity Motor Program from a researcher-implemented program in early childhood centers [28] to a school- or program-staff-led intervention in afterschool settings, a train-the-trainer model [29]. Even though this work is with older children (i.e., elementary school), physical educators or educators with some background in movement, and still includes some ongoing research support, this work is encouraging and demonstrates the timeliness of research efforts to create interventions that fit within the school setting.

Early childhood education centers have unique challenges that must be addressed when creating interventions that could be completed in this setting without external support. In the United States, research supports that teachers in early childhood education have little knowledge about movement guidelines and the importance of structured movement and FMS-building movements in early childhood [30]. This finding mirrors meta-analytic work from a more global perspective [31]. In their systematic review and meta-analyses of >2,300 educators in >260 centers, Jerebine et al [31] reported the two largest barriers early childhood educators face in implementing movement programs are opportunity and capability. Therefore, interventions created for this population should be designed to address these barriers. These programs should fit within current gross motor opportunities within the school and provide educators with training and resources whilst simultaneously limiting the additional burdens on teachers or school staff.

To address these barriers while still creating evidence-based interventions, we propose a change in the modality in which the intervention is delivered. e:health and m:health interventions- interventions that are delivered electronically (e:health) or with the use of mobile devices (m:health) are powerful tools and could be highly effective modalities to deliver motor skill interventions in school settings. These interventions may be effective at improving children’s physical activity behaviors [32, 33], and, currently, there are several m:health interventions that have improved health outcomes in children such as weight outcomes [34] and motor skills and physical activity in young children [35, 36]. The Promoting Lifelong Activity in Youth (PLAY) project is an app-based intervention delivering 12 hours of theoretically grounded intervention content to children through their parents [35, 36]. Families in the PLAY project reported improvements in the children’s motor skills [36]. Additional research in schools also supports that school-based interventions delivered using these e:health or m:health modalities have positive effects on children’s health behaviors including PA and fruit and vegetable consumption [37]. Thus, e:health and m:health modalities are effective, and more research on how these modalities could be used to deliver FMS and PA interventions in early childhood education settings is needed.

Researchers creating interventions should also carefully consider theoretical underpinnings to be used in their design. Three of the main theories used in FMS interventions include Dynamic Systems Theory, Achievement Goal Theory, and Self-Determination Theory [26]. While there is some evidence to support that theoretically, grounded and atheoretical settings interventions are equally effective for improving motor outcomes [26], researchers should consider additional benefits of grounding programs in theory. Integrating Achievement Goal Theory could lead to increased persistence in the face of difficulty [38], positive attitudes toward learning [39, 40], or belief in the direct positive link between effort and outcome [39, 41]. Therefore, it is arguably better to select and use a theory within the design of intervention programs to help elicit not only FMS gains but also improvements in non-motor outcomes that could advantage the learner. One of the most well-researched theoretical approaches in FMS interventions is integrating Achievement Goal Theory by teaching skills in a mastery-motivational climate [23]. Interventions using mastery-motivational climates have immediate and sustained benefits on children’s movement and health outcomes [23]. These programs also improve psychosocial outcomes (e.g., self-regulation and perceived competence) linked to current health and school readiness [42–44].

Interventions using Achievement Goal Theory interventions vary in terms of dose (ranging from 9 weeks to 9 months [23]. To the best of our knowledge, all but one intervention [45] designed with Achievement Goal Theory has been implemented by trained researchers. In this study, a non-motor expert who was still an external person went into the schools and delivered the program, which was delivered during children’s 30-minute outdoor free play period 3 days a week for 15 weeks (1,350 minutes total) [45]. The nonmotor expert completed a 6-hour training prior to the intervention and was responsible for demonstrating all motor skill stations as well as setting up skill stations on the playground. The non-motor expert did not provide any additional feedback or instruction on the playground. Due to the instructional differentiation between the implementation of this program and other work using Achievement Goal Theory, the authors reported this program a a pseudo-mastery climate. After the intervention, children who completed this program exhibited positive changes in their locomotor skills. This work also reported that the intervention was highly feasible and was implemented correctly the majority of the time (>95% of sessions) [45]. Therefore, FMS interventions implemented by non-motor experts in a pseudo-mastery climate might be an important approach to addressing current limitations of the scope of sustainability and scalability. More research in this area is warranted.

There is a particular need for interventions to promote FMS and PA in children who are at risk for current or future health disparities. There are several risk factors associated with poorer FMS and PA in preschoolers, including being from a family with lower SES or an ethnic minority [19, 46–50]. This discrepancy is alarming as these preschoolers are also at risk for other health disparities, including unhealthy weight status [51, 52], inflammation [53], and poorer future cardiovascular health [49]. Additionally, children from low-income families are less prepared for school and underperform compared with children from non-low-income families [54–56]. Movement is central or strongly associated with all these outcomes [57–63]. supporting the need for interventions to promote both FMS and PA specifically in these at-risk populations.

In conclusion, there is a need for FMS interventions that can be implemented in the absence of a researcher’s presence. e:Health and m:health interventions to promote FMS are an emerging and exciting area of research, and more work is needed to examine how these modalities could be used to deliver FMS and PA interventions in early childhood education settings. This research is particularly needed for children who are at risk for future health disparities, such as children in federally subsidized early childhood education centers serving low-income families. This study addresses this need by creating the e:Motor skills At Playtime (MAP) intervention. e:MAP is an FMS intervention grounded in Achievement Goal Theory and is specifically designed to be implemented through an e:health modality within early childhood education settings. The purpose of this pilot study was twofold. First, we will determine the effects of e:MAP on health outcomes, including FMS and PA, in children who are at risk for future health disparities. Secondly, we will gain insight into the usability and potential sustainability of e:MAP within the early childhood education setting by exploring how teachers perceive the program as well as their ability to facilitate the program.

**Goal 1**: Determine the effects of the MAP e:health program on children’s health outcomes (FMS and PA).**Goal 2**: Explore teachers’ perceptions of and ability to facilitate the MAP e:health program within an early childhood education setting.

## 2. Materials & methods

### 2.1. Sample

All children enrolled in preschool classrooms at a single Head Start/Great Start Preschool in Michigan will be recruited. Based on initial MAP work [45], we completed a sample size calculation using an alpha level of 0.05 and a desired power of 80% when comparing the two groups to detect an effect size of Cohen’s d = 0.8 [64]. This estimated effect size represents a meaningful change in children’s motor skills and is higher than meta-analytic reports of average effects sizes from motor interventions [18, 22]. The calculation yielded a minimum of 54 children needed (27 per group). To account for 20% lost to follow-up, we will recruit 32 children per group. We will try our best to minimize the loss of follow-up, and this extra recruitment will help us maintain statistical power with any unexpected smaller detectable group differences in the outcome. Due to the nature of research in a school setting, children will be randomized at the level of the classroom. We will recruit from a minimum of 6 classrooms.

To be enrolled, children must meet the following at the time of study enrollment: 3.5–5.0 years old, able to understand simple verbal instructions in English, and be physically capable of completing the motor skills assessment. Children who have a physical or intellectual impairment that would inhibit them from successfully completing the motor skill assessment will be excluded.

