### 2.8 Planned analyses

Whole-study and group-specific descriptive statistics, including frequencies and percentages of categorical variables, along with mean and standard deviation of continuous variables, will be computed to summarize the sample characteristics. Between-group comparisons will be conducted at baseline to evaluate the success of randomization using two-sample t-tests. The post-intervention trajectory of FMS and PA will be assessed for any group differences, and we will use multilevel linear mixed effect models or generalized linear mixed effect models to determine covariate-adjusted differences between the MAP group and control group after the intervention, controlling for the established influence of sex, age, and anthropometrics on child outcomes [10, 70, 71]. Besides the main effect of each variable, the interaction term between intervention and sex will also be evaluated to investigate whether the intervention had a differential effect for boys and girls.

In regard to teacher outcomes, we will use a dependent sample t-test to explore if there are changes in teachers’ perceptions of the program at posttest. Teacher’s ability to facilitate the program will be reported as a percentage of sessions where teachers correctly executed MAP.

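### The 80% power in section 2.1 rests on independently randomised children, but classrooms are randomised (minimum six), so the claim is not supported

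*Protocol article*

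**What the plan says.** Section 2.1 (Sample) gives a complete sample size calculation. Alpha is 0.05, and the target is "a desired power of 80% when comparing the two groups to detect an effect size of Cohen’s d = 0.8". The result is 54 children, 27 per group. The only inflation is to 32 per group, for 20% loss to follow-up. The section adds that the extra recruitment will help to keep power if the difference proves smaller than expected. It also says that the assumed effect "is higher than meta-analytic reports of average effects sizes from motor interventions".

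The same paragraph then sets the unit of allocation: "children will be randomized at the level of the classroom. We will recruit from a minimum of 6 classrooms". It mentions no ICC, design effect, classroom size or number of classrooms per arm in connection with the calculation. Section 2.1.1 stops recruitment at 90 children.

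For the analysis, section 2.8 says that "we will use multilevel linear mixed effect models or generalized linear mixed effect models". The covariates that it names are sex, age and anthropometrics.

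**The concern.** Children in one classroom share a teacher, a playground routine and, here, the way the programme is delivered. Their outcomes are likely to be correlated, and the arm comparison is made between classrooms. Two things then lower power relative to a trial of independent children. The variance of the difference grows by the design effect. And with six classrooms the between-classroom variance is estimated on about 4 degrees of freedom, where the independent-children test has 52.

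This is not detail left out of a condensed article. The article reports a full calculation, and that calculation belongs to a different design. Goal 1 is to determine the programme's effects on motor skills and physical activity. A null result read against a stated 80% could be taken as evidence of no large effect when the data could not exclude one. The effect size offers no slack either, since section 2.1 itself places d = 0.8 above the usual range.

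**Working it through.** **Inputs from section 2.1:** alpha 0.05 (sidedness not stated, two-sided taken), power 80%, d = 0.8, 27 per group, 20% loss, 32 recruited per group, at least 6 classrooms. **From section 2.1.1:** cap of 90 children. **Assumed, because the article does not give it:** ICC from 0.01 to 0.20; equal classroom sizes; three classrooms per arm at the minimum.

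**1. Reproduce the plan's figure.** For a two-sided two-sample t-test with n independent children per group, the noncentrality is d × √(n/2) on 2n − 2 degrees of freedom. At d = 0.8, n = 26 gives 80.7% power and n = 27 gives 82.2%. A one-sided test would need only about 20 or 21. The stated 27 is therefore the independent-children answer within one child per group. The spare margin is 27/26 = 1.04, which equals the design effect at an ICC of about 0.005 with 9 per classroom (1 + 8 × 0.005 = 1.04).

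**2. Check for a reserve in the dropout step.** After 20% loss, 32 × 0.8 = 25.6 remain per group, below 27. Full inflation would be 27/0.8 = 33.75, so 34. Nothing is left over for clustering.

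**3. Power under classroom randomisation.** With k classrooms per arm and m analysed children in each, the design effect is DE = 1 + (m − 1) × ICC, the standard error of the difference in SD units is √(2 × DE/(k × m)), and the noncentrality is 0.8 divided by that. It is compared with 1.96 (large-sample z) or with t on 2(k − 1) degrees of freedom. For k = 3, m = 9 (27 per arm), without baseline adjustment:

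| ICC (assumed) | DE | Effective n per arm | Standard error | Power, z | Power, t on 4 df | Detectable d at 80%, 4 df |
|---|---|---|---|---|---|---|
| 0.01 | 1.08 | 25.0 | 0.283 | 81% | 57% | 1.06 |
| 0.05 | 1.40 | 19.3 | 0.322 | 70% | 47% | 1.21 |
| 0.10 | 1.80 | 15.0 | 0.365 | 59% | 39% | 1.37 |
| 0.20 | 2.60 | 10.4 | 0.439 | 45% | 29% | 1.65 |

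Example at ICC 0.05: DE = 1 + 8 × 0.05 = 1.40; standard error = √(2 × 1.40/27) = 0.322; noncentrality = 0.8/0.322 = 2.48. Even at ICC 0, power on 4 df is 60%, because the critical value is 2.78 in place of about 2.

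**4. What would narrow the gap.** Power at d = 0.8:

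| Scenario | ICC 0.05: z / cluster df | ICC 0.10: z / cluster df |
|---|---|---|
| 6 classrooms, all 32 per arm retained | 75% / 51% | 63% / 41% |
| 6 classrooms, 90 children, no loss | 83% / 59% | 69% / 46% |
| 10 classrooms, 27 per arm | 76% / 65% | 69% / 58% |
| 10 classrooms, 90 children, no loss | 89% / 80% | 81% / 70% |

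Adjustment for the baseline outcome multiplies the variance by about 1 − r², where r is the pre-post correlation (assumed, and applied at both levels). With six classrooms of 9 on 4 df, r = 0.5 gives 69% at ICC 0.01 and 58% at ICC 0.05; r = 0.7 gives 84% and 74%.

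**5. Type I error, only if z were used.** In 40,000 simulated trials per ICC (six classrooms of 9, between-classroom variance truncated at zero, cut-off 1.96), the rejection rate under no effect was about 5% at ICC 0.01, 7% at 0.05, 8% at 0.10 and 11% at 0.20.

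**The case against.** Four points can be made for the plan.

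- **Six is a floor.** A reader might infer that exactly six classrooms take part and that 4 degrees of freedom are fixed. The article does not say so. Ten classrooms with the full 90 children would reach about 80% on cluster degrees of freedom at ICC 0.05. This stands as a limit on the size of the shortfall. It does not rescue the claim: six is all the article guarantees, 90 is a cap and not a target, and ten classrooms with the planned 27 per arm give 65%.
- **Pretest data exist.** Motor skills and activity are measured before randomisation, and using them could recover much of the loss. This also stands in part. But section 2.1 takes no credit for it, and section 2.8 does not list the baseline outcome among its covariates.
- **The analysis is already multilevel.** A random effect for classroom can protect validity; it cannot supply power. A reader might infer that the planned p-values will be too small. The article does not support that: section 2.8 names no z-based test, and the method for degrees of freedom may sit in an analysis plan that is not shown. Inflation would arise only if z were used and the ICC were not near zero.
- **It is a pilot.** The label is consistent, and the conclusion calls for larger samples. Yet section 2.1 sets a formal 80% target, and the stated limitations mention neither power nor the number of classrooms.

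**Conclusion.** The point holds for the stated power. The arithmetic is sound for independent children; the fault is that this is not the design. At the guaranteed minimum of six classrooms, with 27 analysed per arm and no baseline adjustment, power at d = 0.8 lies between 45 and 81% by z and between 29 and 57% on 4 degrees of freedom, over an assumed ICC of 0.20 down to 0.01.

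These figures are conditional and should not be read as the true power of the trial. At ICC 0.01 clustering itself costs almost nothing (81% by z), and the fall to 57% comes from the few clusters. A larger number of classrooms or a strong baseline covariate could bring power near or above 80% in favourable cases. What can be said firmly is that section 2.1 states 80% without any of the assumptions needed to support it.

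**What to change.** **Section 2.1.** Replace the 80% statement with power and detectable difference under classroom randomisation. Give them for the minimum of six classrooms and for the number expected, with the expected analysed children per classroom, a stated ICC range (for example 0.01 to 0.20) and cluster-based degrees of freedom. State any credit for baseline adjustment as an assumption, with the pre-post correlation used. Present Goal 1 as an estimate with a 95% confidence interval, and say that a null result would be inconclusive.

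**Section 2.8.** State that the arm effect is tested in a model with a classroom random intercept, the baseline outcome as covariate, and small-sample degrees of freedom such as Kenward-Roger.

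**Cost.** A rewritten passage in 2.1 and a sentence in 2.8, with no extra children or visits. The downside is a less favourable stated power and wider intervals.

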### 2.1.1 Recruitment

Study recruitment will begin in August 2024 and be completed in three ways: (1) by teachers using approved scripts during school home visits, (2) by the research team during parent/school open house events, and (3) through materials distributed through backpacks during the first month of school. Students will be enrolled on a first-come, first-served basis. If we have recruited 90 children, recruitment will end, and no additional students will be enrolled.

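### Recruiting 32 per group does not cover the stated 20% loss: it leaves about 51 of 64 children, below the plan's own minimum of 54

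*Protocol article*

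**What the plan says.** Section 2.1 (Sample) of the protocol article builds the sample size in three steps.

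- The inputs are a significance level of 0.05, 80% power and a comparison of two groups "to detect an effect size of Cohen’s d = 0.8".
- The result is given as "The calculation yielded a minimum of 54 children needed (27 per group").
- The allowance for attrition is "To account for 20% lost to follow-up, we will recruit 32 children per group".

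The next sentence begins with the intention to keep loss low, and continues that "this extra recruitment will help us maintain statistical power with any unexpected smaller detectable group differences in the outcome".

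The Methods paragraph of the abstract carries the total forward: "We will recruit at least 64 children". Section 2.1.1 (Recruitment) sets a ceiling: "If we have recruited 90 children, recruitment will end, and no additional students will be enrolled".

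**The concern.** The minimum, the expected loss and the recruitment target are all fixed in the same paragraph, and they do not fit together. A trial that enrolled exactly 64 children and lost exactly the planned 20% would meet its recruitment target and still miss its stated minimum. This is not a detail that an analysis plan could supply, because no further specification makes 80% of 32 reach 27.

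The following sentence compounds the problem. It gives the same five extra children per group a second purpose, protecting power if the group difference is smaller than expected. If the assumed loss occurs, those five are used up and none remain for that purpose. This is relevant because section 2.1 itself says that d = 0.8 is above the average effect in meta-analyses of motor interventions, so a smaller effect is a realistic prospect.

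**Working it through.** **Inputs** (section 2.1 unless noted): alpha 0.05; power 80%; d = 0.8; minimum 27 per group, 54 in total; loss 20%; target 32 per group, 64 in total. The ceiling of 90 is from section 2.1.1. The text does not say whether the test is one- or two-sided; two-sided is assumed.

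**1. The plan's base figure.** A two-sided two-sample t-test at these inputs needs 25.52, so 26 per group (52 in total). The normal approximation gives 25. The stated 27 is one per group above the t-test figure, so it is reproduced closely, on the cautious side. A one-sided test needs only about 20 to 21 per group and does not reproduce it.

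**2. Does 32 per group survive 20% loss?**
- Per group: 32 × (1 − 0.20) = 25.6, against 27.
- In total: 64 × 0.80 = 51.2, against 54.

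**3. What loss does 32 per group tolerate?** (32 − 27)/32 = 5/32 = 15.6%. For the total, (64 − 54)/64 = 15.6%.

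**4. What does 20% loss require?** n = 27/(1 − 0.20) = 33.75, rounded up to 34 per group, 68 in total. Check: 34 × 0.80 = 27.2, which meets 27. The gap is 2 per group, 4 in total.

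**5. Where 32 may come from.** 27 × 1.2 = 32.4, which rounds to 32. The unrounded t-test figure also leads there: 25.52/0.8 = 31.9. The printed base is 27, and from 27 only the multiplication gives 32, but the document states neither route.

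**6. Effect on power** (two-sided t-test, independent children, d = 0.8):

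| Evaluable per group | Situation | Power | Detectable d at 80% power |
|---|---|---|---|
| 32 | no loss | 88.3% | 0.71 |
| 27 | stated minimum | 82.2% | 0.78 |
| 26 | 6 of 32 lost (18.8%) | 80.7% | 0.79 |
| 25.6 | exactly 20% lost | 80.1% | 0.80 |
| 25 | 7 of 32 lost (21.9%) | 79.1% | 0.81 |

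At the planned loss the detectable effect is the design effect itself, so there is no reserve for smaller differences. Some reserve exists when loss is lower, reaching d = 0.71 with no loss at all.

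**The case against.** The best defence is that the shortfall has little consequence. The design requirement is 80% power at d = 0.8, and 27 per group is slightly more than that needs. After 20% loss, power on the same basis is still about 79% to 80%. This stands, and it limits the weight of the point: what is missed is the printed minimum of 54, while the power target behind it is met or missed by about one percentage point.

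Second, 64 is a floor. Section 2.1 intends to approach all children enrolled in the preschool classrooms, and recruitment closes only at 90, where 90 × 0.80 = 72 would comfortably exceed 54. This also stands: actual enrolment may well cover the gap. But a floor is the number that must suffice by itself, and this one does not.

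Three stronger readings are tempting and are not supported.

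- A reader might infer that the authors certainly multiplied by 1.2 where they should have divided by 0.8. That is the likelier explanation from a base of 27, but no formula is given and a second route also yields 32.
- A reader might infer that the sentence on smaller differences is simply untrue. It opens with minimising loss and promises only help, with no fixed margin. If loss is held below 15.6%, more than 27 per group remain and the detectable difference does fall. The sentence lacks a condition; it does not need to be deleted.
- A reader might add the effect of randomising classrooms to the size of this error. That is a separate matter. The power figures here treat children as independent because they check the article's calculation on its own apparent basis; they do not describe the power of the mixed-model analysis in section 2.8 (Planned analyses).

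**Conclusion.** The statement is wrong as written. With 20% loss, 32 per group leaves 25.6 per group, about 51 of 64, against a stated minimum of 27 per group and 54 in total. The target tolerates 15.6% loss; a true 20% allowance from 27 needs 34 per group, 68 in total. The shortfall is 4 children overall.

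The attrition arithmetic uses only the article's own figures and needs no assumption. The power figures assume a two-sided, unadjusted t-test on independent children; on that basis the cost is about 2 to 3 percentage points relative to the stated minimum, leaving power at about 79% to 80%. This is a small but definite inconsistency in the sample-size statement. It does not show that the trial is materially underpowered for this reason.

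**What to change.** Choose one of two corrections in section 2.1.

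- Keep 32 per group (64) and state that it preserves 54 evaluable children only up to about 15.6% loss, or equivalently that 20% loss would leave about 51. This needs no additional children and no change to the abstract.
- State 34 per group (68 in total) as the number that covers 20% loss, and change the abstract's floor from 64 to 68. This is four more children, already inside the ceiling of 90.

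In either case, give the inflation formula, and qualify the sentence on smaller differences so that it says the extra children help only to the extent that loss stays below the tolerated rate. The cost is one number or one clause, plus one qualifying phrase; the design and the analysis are unaffected.
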